### 3.4.7 SPONSOR Responsibility for Reporting Adverse Experiences

All adverse experiences collected via study guidelines will be reported to regulatory agencies, IRB/IECs, and investigators in accordance with all applicable global laws and regulations.

The investigator is responsible for obtaining Review Board approval of the protocol, as well as approval of all subsequent major changes, in compliance with local law. Copies of these approvals must be forwarded to the SPONSOR.The IRB will comply with all federal, state, and local laws. Particular attention is drawn to the Food and Drug Administration Regulations for Institutional Review Boards (21 CFR, Part 56), and the International Conference on Harmonisation (ICH) Guidelines for Good Clinical Practices for IRB/IEC Committees. Copies of relevant information derived from these guidelines are included in the administrative binder. The investigator is responsible for obtaining initial and continuing review (at intervals not less than once per year) of the study by an IRB. Written approval from the IRB must be forwarded to the SPONSOR before clinical supplies will be shipped. For continuing studies, written approval from the IRB must be sent to the SPONSOR at intervals not to exceed 1 year.

The investigator shall also obtain from the IRB and submit to the SPONSOR, a signed statement indicating that it complies with Good Clinical Practices. A sample IRB Compliance letter is included in the administrative binder .

For both Merck and non-Merck studies, the SPONSOR will promptly be advised of any regulatory agency inspection of the institution or IRB/IEC conducted within the past 2 years or during the course of this study. Final results (i.e., final observations and responses) of such inspections should be promptly communicated to the SPONSOR. Any “SPONSOR-related” confidential information (SPONSOR name, study titles, compound identifiers, etc.) should be redacted via correction fluid or other appropriate methods from communications regarding inspection results for non-Merck studies.

The SPONSOR will promptly be advised of any IRB/IEC inspection of the investigator for a Merck-sponsored study during the course of this trial. The notification and outcome [written report(s) and response(s) when available] of such inspections should be promptly communicated to the SPONSOR by the investigator. The investigator will maintain copies of all IRB/IEC inspection reports and responses in the corresponding study file(s).

## 3.5 Data Analysis

This section outlines the statistical analysis strategy and procedures for the study. No separate Statistical Analysis Plan (SAP) will be issued for this LTFU study.

### 3.5.1 Responsibility for Analyses/In-House Blinding

The statistical analysis of the data obtained from this study will be the responsibility of the Late Development Statistics department of the SPONSOR. As stated in Section , treatment assignment blinding of study subjects and personnel is not applicable to this LTFU study.

### 3.5.2 Hypotheses/Estimation

Objectives and hypotheses of the study are stated in Section 2.1.

### 3.5.3 Analysis Endpoints

The HPV-related disease endpoints that will be addressed in this LTFU study are as defined in Sections 2.5.2 and 2.5.3 of this protocol.

### 3.5.4 Analysis Populations

The analysis populations that will be examined in this LTFU study are the PPE, HNRT, and FAS populations that are described in Section 2.7 of this protocol.

### 3.5.5 Statistical Methods

Because there is no placebo group in this LTFU study, vaccine efficacy (VE) estimation as described in Section 3.3.1 of the V501-019 SAP does not apply to this LTFU study. In lieu of VE estimates, cumulative incidence probabilities (or percents) based on non-parametric life-table methods will be computed for each of Cohorts 1 and 2 as described in Section of this protocol. The cohort-specific cumulative incidence probabilities will be put into context against the GARDASIL™ group- and placebo group-specific cumulative incidences observed during the base study. Details are provided in Section of this protocol.

As stated in Section 2.7, three analyses are planned corresponding to the time when all participating subjects have completed each of the scheduled visits at Years 6, 8, and 10 relative to the base study Day 1. Figure 3-1 shows key analysis-related time points and time intervals relative to the Years 6, 8, and 10 analysis time points in the LTFU study. Section of this protocol describes the observational comparisons relating to effectiveness that are feasible within the context of this LTFU study based on the key time points and time intervals shown in Figure 3-1.

Figure 3-1

Schematic Representation of Key Analysis-Related Time Points and Time Intervals
Relative to the Years 6, 8, and 10 Analysis Time Points in the LTFU Study

#### 3.5.5.1 Statistical Methods for Assessment of Effectiveness

Effectiveness will be assessed by computing cohort-specific incidences during the LTFU study as shown in Figure 3-1 and these LTFU incidences will be put into context against the incidences observed during the base study as summarized in Table 3-4. The cumulative incidence probabilities (or percents) based on non-parametric life-table methods, not the incidence rate (per 100 person-years), will be the primary metric that will be used for computing the cumulative incidences that will be used in observationally assessing effectiveness as summarized in Table 3-4.

Cohort 1

- At the Year 6 time point, cumulative incidence from Day 1 to Year 6 of HPV 6/11/16/18-related disease endpoints will be computed and reported. There are no corresponding 6-year cumulative incidences from the base study. Also at the Year 6 timepoint, cumulative incidences (of HPV 6/11/16/18-related disease endpoints) from Year 4 to Year 6, representing a 2-year incidence, will be computed and reported. This 2-year incidence will be evaluated in the context of the 2-year incidence from Day 1 to Year 2, and from Year 2 to Year 4, observed during the base study. Note that a 2-year period in the context of accumulating HPV 6/11/16/18-related disease endpoints is a very short time, the incidence is expected to be low, and the estimate of the cumulative incidence is not expected to have a high degree of precision.
- The continuing effectiveness of vaccination in Cohort 1 at the Year 8 time point will be assessed by evaluating the 4-year incidence in Cohort 1 from Years 4 to 8 (see Figure 3-1 and Table 3-4) in the context of Cohort 1's 4-year incidence from Day 1 to Year 4 during the base study. Similar 4-year incidences from Day 1 to Year 4 and from Years 4 to 8 are an indication of continuing vaccine effectiveness.
- The continuing effectiveness of vaccination in Cohort 1 at the Year 10 time point will be assessed by evaluating the 4-year incidence in Cohort 1 from Years 6 to 10 in the context of Cohort 1's 4-year incidence from Day 1 to Year 4 of the base study, and Cohort 1's 4-year incidence from Year 4 to Year 8. Similar 4-year incidences from Day 1 to Year 4, from Years 4 to 8, and from Years 6 to 10 are an indication of continuing vaccine effectiveness.

Cohort 2

- At the Year 6 time point, Cohort 2 subjects would have had approximately only a 1-year follow-up relative to the date of their vaccine dose 1 injection. A 1-year follow-up time post-dose 1 is too short for the purpose of accumulating and observing HPV 6/11/16/18-related disease endpoints. No cumulative incidence summaries will be computed for Cohort 2 at the Year 6 time point.
- The effectiveness of vaccination in Cohort 2 at the Year 8 time point will be assessed by evaluating the incidence from vaccine dose 1 to Year 8, which for Cohort 2 represents a 3-year incidence post-dose 1 (see Figure 3-1 and Table 3-4), in the context of the GARDASIL™ group's 3-year incidence from Day 1 to Year 3 during the base study. The 3-year duration (instead of 4 years) for trying to capture and observe a HPV-related disease endpoint is a limitation of the Year 8 effectiveness assessment in Cohort 2.
- The effectiveness of vaccination in Cohort 2 at the Year 10 time point will be assessed by evaluating the 4-year incidence in Cohort 2 from Years 6 to 10 in the context of the GARDASIL group's 4-year incidence from Day 1 to Year 4 during the base study. Similar 4-year incidences from Day 1 to Year 4 in the base study GARDASIL™ group and from Years 6 to 10 in Cohort 2 is an indication of vaccine effectiveness in Cohort 2.

Table 3-4

Summary of Effectiveness Measures in the LTFU Study and the Corresponding
Incidence Measures in the Base Study
(By Analysis Time and Cohort)

| Analysis Time  Cohort | Incidence During LTFU Study | vs. | Incidence During Base Study |
| --- | --- | --- | --- |
| Year 6 |  |  |  |
| Cohort 1 | 6-year incidence (Day 1 to Year 6)  2-year incidence (Years 4 to 6) | vs.  vs. | N/A  2-year incidence† in Cohort 1§; 2-year incidence† in the Cohort 2║;  2-year incidence† in the Placebo group. |
| Year 8 |  |  |  |
| Cohort 1 | 8-year incidence (Day 1 to Year 8)  4-year incidence (Years 4 to 8) | vs.  vs. | N/A  4-year incidence‡ in Cohort 1§; 4-year incidence‡ in the Cohort 2║;  4-year incidence‡ in the Placebo group. |
| Cohort 2 | 3-year incidence (Years 5 to 8) | vs. | 3-year incidence¶ in Cohort 2║; 3-year incidence¶ in Cohort 1;  3-year incidence¶ in the GARDASIL™ group. |
| Year 10 |  |  |  |
| Cohort 1 | 10-year incidence (Day 1 to Year 10)  4-year incidence (Years 6 to 10) | vs.  vs. | N/A  4-year incidence‡ in Cohort 1§; 4-year incidence# in Cohort 1; 4-year incidence‡ in the Cohort 2║;  4-year incidence‡ in the Placebo group. |
| Cohort 2 | 5-year incidence (Dose 1 to Year 10)  4-year incidence (Years 6 to 10) | vs.  vs. | N/A  4-year incidence‡ in Cohort 2║; 4-year incidence‡ in Cohort 1;  4-year incidence‡ in the GARDASIL™ group. |
| † Cumulative incidence from Day 1 to Year 2; and also cumulative incidence from Year 2 to Year 4.  ‡ Cumulative incidence from Day 1 to Year 4.  § Subjects from Colombia randomized to the GARDASIL™ group.  ║ Subjects from Colombia randomized to the placebo group.  ¶ Cumulative incidence from Day 1 to Year 3.  # Cumulative incidence from Years 4 to 8.  LTFU = Long term follow-up; N/A = Not available. There is no corresponding incidence during the base study. | | | |

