The primary analysis approach for Cohort 1 will be per-protocol-efficacy (PPE), as defined during the base study. To be eligible for this population, subjects must (i) have received 3 doses of GARDASIL™ within 1 year, and (ii) have no protocol violations. Subjects will be considered cases related to a given HPV type provided the subject was negative to the respective HPV type by serology and PCR prior to vaccination (i.e., during the base study) and PCR negative through Month 7. For purposes of endpoint definition, only the Pathology Panel diagnosis will be considered. Supportive analyses will be done for the group naïve to the relevant HPV type (HNRT) and full analysis set (FAS). The HNRT population consists of all subjects who received at least 1 vaccination and were seronegative and PCR negative to the relevant type prior to vaccination. The FAS population includes all vaccinated subjects, regardless of HPV status. Subjects who were cases of the relevant endpoint during the main study will not be included in the LTFU analyses of that endpoint.

The base study PPE population definition can not be applied to Cohort 2 subjects due to absence of HPV serology and PCR status information on Cohort 2 subjects at the time immediately before injection of vaccine Dose 1, and absence of HPV PCR status at "Month 7", i.e., at 1-month post vaccine Dose 3. Therefore, the analysis on Cohort 2 subjects will be done on the FAS population.

The sample size for the effectiveness and immunogenicity components of the LTFU study is fixed by the number of Protocol 019 base study and 019-10 study participants from Colombia who are eligible and willing to participate in the LTFU study. There are approximately 800 subjects in each of Cohorts 1 and 2 in the participating sites in Protocol 019-20 who will contribute extension study data. Given this relatively small sample size, it is important to note that the expected number of endpoint cases that can potentially be observed over the LTFU period is low. For example, the incidence rate of HPV 16/18-related CIN2/3 in the per-protocol placebo group during the base study was 0.1 per 100 person-years. Table 2-1 illustrates incidence rate estimates and confidence intervals for the indicated numbers of cases that can potentially be observed during the LTFU period. It is clear that in many cases, the confidence intervals do not exclude the placebo incidence rate of 0.1.

Table 2-1

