|  | Year 3 | 3 | 0.39 | (0.13, 1.20) | 6 | 0.77 | (0.35, 1.71) |
|  | Year 4 | 3 | 0.39 | (0.13, 1.20) | 7 | 0.90 | (0.43, 1.89) |
| HPV 16/18-related CIN 2/3 or worse |  |  |  |  |  |  |  |
| All base study subjects | Year 2 | 17 | 0.94 | (0.58, 1.50) | 19 | 1.03 | (0.66, 1.61) |
|  | Year 3 | 21 | 1.17 | (0.76, 1.79) | 23 | 1.27 | (0.84, 1.90) |
|  | Year 4 | 21 | 1.17 | (0.76, 1.79) | 27 | 1.53 | (1.08, 2.30) |
| Colombia cohort | Year 2 | 7 | 0.90 | (0.43, 1.88) | 8 | 1.02 | (0.51, 2.02) |
|  | Year 3 | 10 | 1.32 | (0.71, 2.43) | 9 | 1.16 | (0.60, 2.20) |
|  | Year 4 | 10 | 1.32 | (0.71, 2.43) | 13 | 1.76 | (1.08, 3.28) |
|  |  |  |  |  |  |  |  |
| CIN 2/3 or worse Due to Any HPV Type |  |  |  |  |  |  |  |
| All base study subjects | Year 2 | 48 | 2.63 | (1.98, 3.47) | 34 | 1.86 | (1.33, 2.58) |
|  | Year 3 | 55 | 3.04 | (2.34, 3.93) | 38 | 2.09 | (1.52, 2.86) |
|  | Year 4 | 59 | 3.28 | (2.59, 4.29) | 48 | 2.75 | (2.15, 3.79) |
| Colombia cohort | Year 2 | 20 | 2.58 | (1.67, 3.96) | 13 | 1.67 | (0.97, 2.86) |
|  | Year 3 | 23 | 2.99 | (1.99, 4.46) | 15 | 1.94 | (1.18, 3.21) |
|  | Year 4 | 24 | 3.13 | (2.15, 4.77) | 22 | 3.06 | (2.13, 4.98) |
| N = Number of subjects randomized to the respective vaccination group who received at least 1 injection.  CI = Confidence interval; CIN = Cervical intraepithelial neoplasia; EGL = External genital lesions; HPV = Human papillomavirus. | | | | | | | |

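### Cohort 2: similarity to the base-study GARDASIL group cannot indicate effectiveness on HPV 16/18 CIN 2+, because in the full analysis set that group has no established difference from placebo

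*Protocol*

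**What the plan says.** Protocol section 3.5.5.1 deals with Cohort 2 at two analyses that yield incidences.

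- **Year 10.** The 4-year incidence over Years 6 to 10 is set against the GARDASIL group's Day 1 to Year 4 incidence, and similar values "in the base study GARDASIL™ group and from Years 6 to 10 in Cohort 2 is an indication of vaccine effectiveness in Cohort 2". No margin or definition of similar is given.
- **Year 8.** The 3-year incidence after dose 1 is evaluated "in the context of the GARDASIL™ group's 3-year incidence from Day 1 to Year 3 during the base study". The bullet names the short window as a limitation and contains no similarity sentence.

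Section 2.7 explains why the per-protocol population cannot be built for these women and concludes: "Therefore, the analysis on Cohort 2 subjects will be done on the FAS population". It also says: "The FAS population includes all vaccinated subjects, regardless of HPV status". Section 3.5.5.1 does not name the population of the base-study reference. The FAS follows, since it is the only population available for a like-for-like comparison.

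HPV 16/18-related CIN 2+ is one of the two effectiveness endpoints in sections 2.1.3 and 2.5.2. Table 3-6 (section 3.5.7) gives its FAS results as cases, percent and 95% CI, GARDASIL then placebo. All subjects at Year 4: "21 | 1.17 | (0.76, 1.79) | 27 | 1.53 | (1.08, 2.30". Colombia at Year 3: "10 | 1.32 | (0.71, 2.43) | 9 | 1.16 | (0.60, 2.20".

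Table 3-4 also lists Cohort 2's own base-study (placebo-period) incidence and Cohort 1's incidence as comparators for Cohort 2. The text attaches no reading to either.

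**The concern.** Inferring effectiveness from similarity to a vaccinated group works only if that group differs from placebo on the same endpoint and in the same population. Otherwise a result similar to vaccine may equally be a result similar to placebo.

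The FAS includes women already infected at vaccination, which dilutes any preventive effect. For HPV 16/18 CIN 2+ the FAS percentages of the two arms lie close together, and at 3 years in Colombia the vaccine arm is the higher. At stake is what the study may conclude about women vaccinated at 29 to 50 years of age. On this endpoint the Year 10 reading could report an indication of effectiveness whether or not the vaccine worked in them.

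**Working it through.** **Inputs.** FAS cases and life-table percentages from Table 3-6. Cohort 2 size: about 800 (section 2.7); 600 to 800 is used here to allow for non-participation (assumption). Effective denominators are back-calculated as cases / percent, for example 21 / 0.0117 = 1,795, 27 / 0.0153 = 1,765, 10 / 0.0132 = 758 and 13 / 0.0176 = 739.

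**Reproducing the table.** Complementary log-log interval with SE of the log cumulative hazard = 1/√cases. For GARDASIL, 21 cases and 1.17%: −ln(1 − 0.0117) = 0.01177, multiplied by exp(±1.96/√21) = exp(±0.428), gives 0.76% to 1.79%, as stated. For placebo, 27 cases and 1.53%, it gives 1.05% to 2.22% against the stated 1.08% to 2.30%. The shortcut ignores late censoring, so a small gap is expected.

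**Vaccine v placebo in the FAS.** RR = ratio of percentages; SE(log RR) = √(1/c1 − 1/n1 + 1/c2 − 1/n2). Example, all subjects at Year 4: 1.17/1.53 = 0.76; SE = √(1/21 − 1/1795 + 1/27 − 1/1765) = 0.289; 95% CI 0.43 to 1.35.

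| Endpoint, FAS | GARDASIL | Placebo | RR (95% CI) | Fisher p |
|---|---|---|---|---|
| HPV 16/18 CIN 2+, Year 4, all | 21, 1.17% | 27, 1.53% | 0.76 (0.43–1.35) | 0.39 |
| HPV 16/18 CIN 2+, Year 4, Colombia | 10, 1.32% | 13, 1.76% | 0.75 (0.33–1.70) | 0.53 |
| HPV 16/18 CIN 2+, Year 3, all | 21, 1.17% | 23, 1.27% | 0.92 (0.51–1.66) | 0.88 |
| HPV 16/18 CIN 2+, Year 3, Colombia | 10, 1.32% | 9, 1.16% | 1.14 (0.46–2.78) | 0.82 |
| Composite, Year 4, all | 39, 2.13% | 60, 3.33% | 0.64 (0.43–0.95) | 0.03 |
| Composite, Year 4, Colombia | 18, 2.32% | 38, 4.94% | 0.47 (0.27–0.82) | 0.006 |
| Composite, Year 3, all | 36, 1.95% | 51, 2.79% | 0.70 (0.46–1.07) | 0.10 |
| Composite, Year 3, Colombia | 16, 2.06% | 29, 3.70% | 0.56 (0.30–1.02) | 0.07 |

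The composite is the table's HPV 6/11/16/18-related CIN or EGL, taken as the nearest match to the first endpoint of section 2.5.2.

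**How often would a Cohort 2 with no vaccine effect look similar?** Expected HPV 16/18 CIN 2+ cases in 800 women over 4 years are 9.4 at 1.17%, 12.2 at 1.53% and 14.1 at 1.76%. Take similar as Fisher p of at least 0.05 (assumption) and sum exact binomial probabilities for 600 to 800 women:

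- True rate 1.76% (Colombian placebo) against GARDASIL 21/1,795: 82 to 88%. Against Cohort 1 (10/758): 97 to 98%.
- True rate 1.17% (vaccine) against GARDASIL 21/1,795: 98 to 99%.
- Three years, true rate 1.16% (Colombian placebo) against GARDASIL 21/1,795: 98 to 99%.
- Composite at 4 years, true rate 4.94%: 2 to 6% against GARDASIL (39/1,831), 12 to 22% against Cohort 1 (18/776).

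A second reading of similar, that the estimate from 800 women falls inside the GARDASIL interval 0.76 to 1.79%, gives 0.55 at a true 1.76%, 0.71 at 1.53% and 0.77 at 1.17%. The size depends on the definition. Under both, similarity on this endpoint is a common finding with no vaccine effect.

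**The case against.** The study is descriptive. It tests no hypothesis, section 2.7 says efficacy cannot be analysed without controls, and section 3.5.7 warns that LTFU incidences will be hard to tell apart from the Table 3-4 comparators. Table 3-4 puts Cohort 2's placebo-period incidence beside the GARDASIL figure, so a reader would see both. Fisher's test is not in the plan.

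Much of this stands. No error rate is at issue, and the percentages above illustrate one definition of similar. But section 3.5.5.1 still fixes in advance how a result will be read, and the only reading it fixes is similarity to GARDASIL. The worked example in section 3.5.7 concerns the per-protocol population and Cohort 1. A warning that differences are hard to detect makes it less safe to treat the absence of one as effectiveness.

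A reader might infer three stronger things that the protocol does not support.

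- **That the vaccine has no effect on this endpoint in the FAS.** The 4-year point estimates favour vaccine by about 24%, with wide intervals.
- **That the problem holds for any window.** Table 3-6 gives only figures counted from Day 1. Between Years 3 and 4 the added cases are 0 vaccine v 4 placebo, both overall (21 to 21, 23 to 27) and in Colombia (10 to 10, 9 to 13). The counts are small, but a contrast later in follow-up is possible.
- **That the similarity rule also governs Year 8.** Its sentence stands in the Year 10 bullet only.

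**Conclusion.** The point holds for HPV 16/18-related CIN 2+ at Year 10. In the FAS the reference group has no established difference from placebo on this endpoint (RR 0.75 to 1.14 across the four comparisons, every interval including 1), so similarity to it is not an indication of effectiveness. A benefit is neither shown nor excluded.

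The point does not extend to the composite at 4 years, where the FAS arms separate. At 3 years the composite's intervals also include 1, so the Year 8 comparison cannot carry an effectiveness reading either, should anyone apply one.

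Assumptions: the base-study reference is the FAS; denominators are back-calculated from life-table percentages; the two arms' estimates are independent; 600 to 800 women contribute. Section 2.7 adds: "Subjects who were cases of the relevant endpoint during the main study will not be included in the LTFU analyses of that endpoint". That exclusion may lower Cohort 2's incidence whatever the vaccine does, which would make similarity easier still to reach.

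**What to change.** In section 3.5.5.1:

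1. Restrict the Year 10 similarity statement for Cohort 2 to the HPV 6/11/16/18 composite.
2. Require it to be read together with an estimated difference or ratio and its 95% CI against Cohort 2's own placebo-period incidence, which Table 3-4 already lists. The interval must allow for uncertainty in both estimates. State that the windows differ (Years 6 to 10 against Day 1 to Year 4) and that base-study cases are excluded from the later one.
3. Report FAS HPV 16/18 CIN 2+ for Cohort 2, and the Year 8 three-year comparison, descriptively, and say that similarity to the GARDASIL group there is not evidence of effectiveness.

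A fixed pass/fail bound, such as an exact upper limit below the Colombian placebo figure of 4.94%, should not be used instead. It treats as known a value whose own interval is 3.73 to 6.99%, and it compares unlike windows. The Colombian placebo increment over Years 2 to 4 is 4.94 − 2.79 = 2.15 points, or about 4.3% over 4 years if constant (assumption). The bound allows at most 19, 23 or 27 cases in 600, 700 or 800 women. With no vaccine effect that is met about 2% of the time at a true 4.94%, but 10 to 11% at 4.3%.

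The cost is wording in section 3.5.5.1 and a note to Table 3-4, with no new data. The downside is that no effectiveness statement for Cohort 2 can rest on FAS HPV 16/18 CIN 2+ or on the Year 8 comparison.

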## 1.5 Sample

The study will enroll ~1,600 subjects who were enrolled in the Protocol 019 base study in Colombia.

• Cohort 1: ~800 of whom were vaccinated with GARDASIL™ at the beginning of the base study and

• Cohort 2: ~800 of whom were vaccinated with GARDASIL™ during the 019-10 extension (i.e., after the conclusion of the base study).

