## 2.7 Statistical Analysis Plan Summary

In the absence of a control group in the LTFU study, it is not possible to perform analyses of efficacy. Instead, effectiveness will be measured in terms of incidence rates of disease, with analyses performed periodically until the end of the follow-up in Protocol 019-20. Three (3) analyses are planned, corresponding to the time when all participating subjects have completed each of the scheduled visits at Years 6, 8, and 10 relative to the base study Day 1. All subjects who received GARDASIL™ within the context of Protocols 019 base study or the 019-10 extension from the participating sites in Colombia will contribute to the effectiveness analyses. At each analysis time point, the cumulative and current (for the current interval) number of cases for each effectiveness endpoint will be counted by analytical cohort. Incidence rates based on accrued person-years of follow-up will be estimated together with a corresponding 95% confidence interval.

As an aid to interpretation, incidence rates observed during the LTFU study will be put in context with corresponding incidence rates observed during the base study to provide an assessment of vaccine effectiveness. If any other new data becomes available during the LTFU which provides relevant information for this study population, from Merck studies or the published literature, that will also be used to contextualize the incidence rates that will be observed during the LTFU study. All LTFU analyses will be specific to time since vaccination, so will be presented separately for Cohort 1 and Cohort 2. Cohort 1 includes subjects vaccinated with GARDASIL™ on Day 1 in the base study. Cohort 2 subjects were allocated to receive placebo during the base study and can be enrolled in the long term follow-up extension following receipt on GARDASIL™ in the first extension (Protocol 019-10).

Exploratory analyses may be done to assess the expected continued protection against recurrent infection in women who were seropositive and PCR negative to the relevant HPV type in the vaccine. Sensitivity analyses may be done to study expected *vs.* observed cases of disease due to recurrent HPV types.

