#### 3.5.5.3 Statistical Methods for Assessment of Immunogenicity

The procedure for estimating geometric mean titers (GMTs) as described in Section 3.3.2 of the V501-019 SAP will be used. GMTs and corresponding 95% confidence intervals of HPV (6, 11, 16, and 18) will be summarized for the time points indicated in Table 3-5.

Table 3-5

Summary of Time Points Post-Vaccine Dose 1 For Which HPV (6, 11, 16, and 18) Titers Will Be Available from the Base Study and LTFU Study

| Cohort | Time from Vaccine Dose 1 (in Months) | | | | | | | | |
| --- | --- | --- | --- | --- | --- | --- | --- | --- | --- |
| 7 | 12 | 24 | 36 | 48 | 60 | 72 | 96 | 120 |
| GARDASIL™ Group (Base study) † | + | + | + | + | + |  |  |  |  |
| Cohort 1 (LTFU study)† | + | + | + | + | + |  | + | + | + |
| Cohort 2 (LTFU study) |  | + |  | + |  | + |  |  |  |
| + indicates that HPV (6, 11, 16, and 18) titers will be available corresponding to the indicated time point in the indicated cohort at the end of the LTFU study.  † Cohort 1 includes subjects enrolled and vaccinated with GARDASIL™ on Day 1 in the base study who continued into LTFU.  LTFU = Long term follow-up. | | | | | | | | | |

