### 3.5.7 Power and Sample Size

As stated in Section 2.7, the sample size for the effectiveness and immunogenicity components of the LTFU study is fixed by the number of Protocol 019 base study participants from Colombia who are eligible and willing to participate in this LTFU study. The expected number of cases that can potentially be observed during the LTFU study based on ~1,600 subjects, together with the number of cases observed in some endpoints during the base study, makes it difficult to statistically differentiate the incidences observed during the LTFU study with the comparator incidences identified in Table 3-4. As an example, Table 3-6 shows the incidences observed during the base study for some selected vaccine HPV type-related disease endpoints in the per-protocol efficacy and full analysis set populations. For the endpoint of HPV 16/18-related CIN 2/3 or worse in the per-protocol efficacy population, the 4-year cumulative incidence (based on life-table estimate) during the base study are as follows:

- 0% in Cohort 1 (i.e., Colombia subjects randomized to the GARDASIL™ group) (the asymptotic standard error of cumulative incidence based on life-table method is 0 due to zero cases observed, therefore, 95% CI of cumulative incidence is not estimable);
- 0.07% (95% CI: 0.01 to 0.47) in the GARDASIL™ group;
- 0.41% (95% CI: 0.19 to 0.92) in the placebo group;
- 0.47% (95% CI: 0.15 to 1.46) among Colombia subjects randomized to the placebo group (i.e., Cohort 2 subjects).

Thus, for the base study 4-year cumulative incidence of HPV 16/18-related CIN 2/3 or worse in the per-protocol efficacy population, the incidence in the GARDASIL™ group is not statistically differentiable from the incidence in the placebo group (either all placebo recipients or only placebo recipients from Colombia). Consequently, it will be difficult to statistically differentiate the 4-year cumulative incidence of HPV 16/18-related CIN 2/3 or worse in the per-protocol efficacy population in Cohort 1 during the LTFU study (either from Years 4 to 8 or Years 6 to 10) from the base study 4-year cumulative incidence in the placebo group (either all placebo recipients or only placebo recipients from Colombia).

Table 3-6

Life-Table Estimate of Cumulative Incidence of HPV 6/11/16/18-Related Disease Endpoints During the Base Study
(Per-Protocol Efficacy and Full Analysis Set Populations)

| Endpoint | Time from Vaccine Dose 1 | GARDASIL™  (N=1,910) | | | Placebo (N=1,907) | | |

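### Cohort 1 is the whole Colombian GARDASIL arm in the effectiveness comparator but only continuing women in Table 3-5, so the similar-incidence reading rests on unstated, unchecked non-informative non-return

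*Protocol*

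**What the plan says.** Protocol Section 3.5.5.1 judges Cohort 1's incidence in Years 4 to 8 "in the context of Cohort 1's 4-year incidence from Day 1 to Year 4 during the base study". It does the same for Years 6 to 10, and takes similar incidences as pointing to continuing effectiveness.

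The documents describe Cohort 1 in several ways:

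- Table 3-4, footnote §, for the base-study comparator: "Subjects from Colombia randomized to the GARDASIL™ group".
- Section 3.5.7, with the base-study result attached: "0% in Cohort 1 (i.e., Colombia subjects randomized to the GARDASIL™ group".
- Section 2.7: "Cohort 1 includes subjects vaccinated with GARDASIL™ on Day 1 in the base study", with no condition on continuing.
- Section 1.5, within the roughly 1,600 women the follow-up will enroll: about "800 of whom were vaccinated with GARDASIL™ at the beginning of the base study".
- Table 3-5, footnote: "Cohort 1 includes subjects enrolled and vaccinated with GARDASIL™ on Day 1 in the base study who continued into LTFU".

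Section 2.7 also counts "All subjects who received GARDASIL™ within the context of Protocols 019 base study or the 019-10 extension" from the participating Colombian sites as contributing to effectiveness. It fixes the sample by eligibility and willingness, and removes base-study cases from the follow-up analysis of the same endpoint. Section 3.2.3.1 requires re-consent. Section 3.5 states that no separate SAP will be issued for this study.

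**The concern.** The Cohort 1 comparison is presented as a group against its own past. The past, however, is measured in every Colombian woman randomized to GARDASIL, and the later years mainly in those who came back. If the women who did not return differ in risk, the later incidence moves with no change in protection. Lower-risk returners could hide waning, and higher-risk returners could mimic it. The protocol plans no comparator limited to continuers and no check of continuers against non-continuers, so a reader of the results could not separate selection from sustained protection.

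**Working it through.** **1. Which women each window covers.** Dividing cases by cumulative incidence in the Colombian GARDASIL rows of Table 3-6 (full analysis set, FAS) recovers the approximate denominator: 12/1.53% = 784 and 20/2.58% = 775 at Year 2; 18/2.32% = 776 at Year 4. The comparator is thus essentially the whole arm of about 800.

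The Year 10 row of Table 3-4 places "4-year incidence‡ in Cohort 1§; 4-year incidence# in Cohort 1" side by side, the first marked § and the second not. Little can be built on that, because the Cohort 2 rows also leave the mark off Day 1 entries for Cohort 1.

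**2. The plan's own follow-up figure.** Table 2-1 assumes full follow-up of 800 women. Taking Years 4 to 10 gives 800 × 6 = 4,800 person-years. Exact Poisson limits per 100 person-years are then:

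| Cases | Rate (95% CI) |
| --- | --- |
| 0 | 0 (0, 0.077) |
| 1 | 0.021 (0.0005, 0.116) |
| 2 | 0.042 (0.005, 0.150) |
| 3 | 0.063 (0.013, 0.183) |

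These reproduce Table 2-1 to its two decimals, so the planning case is near-complete return.

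**3. Effect of selective return.** Let p be the share of the arm that participates and k the risk in non-participants divided by that in participants. Assume a constant hazard and unchanged protection. If participants' risk is R, the whole arm's Day 1 to Year 4 risk is R × (p + (1 − p)k) and the participants' later 4-year risk is R. The apparent ratio of later to earlier incidence is

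1 / (p + (1 − p)k).

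The documents give neither p nor k, so both are assumed:

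| p | k = 0.5 | k = 1 | k = 2 |
| --- | --- | --- | --- |
| 0.9 | 1.05 | 1.00 | 0.91 |
| 0.8 | 1.11 | 1.00 | 0.83 |
| 0.7 | 1.18 | 1.00 | 0.77 |
| 0.6 | 1.25 | 1.00 | 0.71 |

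Example: p = 0.7 and k = 2 gives 1/(0.7 + 0.3 × 2) = 1/1.3 = 0.77. Applied to the FAS figure of 2.32%, the later incidence would be 2.32/1.3 = 1.78%, and a true 1.30-fold rise among returners would look like no change. As p approaches 1, every entry approaches 1.00.

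**4. Where the comparator can move.** In the per-protocol (PPE) rows of Table 3-6, the Colombian GARDASIL group has 0 cases for all three endpoints at Years 2, 3 and 4. Any subset also has 0, so the Cohort 1 comparator is the same under either definition. In FAS it can move: 18 Colombian GARDASIL cases of HPV 6/11/16/18-related CIN or external genital lesions, 2.32% (1.47 to 3.65). The Colombian placebo comparators can also move, with 13 PPE and 38 FAS cases of that endpoint at Year 4.

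**The case against.** For effectiveness, Section 2.7, Table 3-4 and Section 3.5.7 agree. Only the immunogenicity table adds the condition on continuing, in a row labelled as the follow-up study. If all recipients contribute to a life table, non-returners are censored within one cohort and no second population is swapped in. Some observation after Year 4 may also exist for women who never joined, since Section 2.4.1 places the end of the base study at about Year 5. This stands, and it limits the point: the later windows are mainly, not exclusively, returners, and the issue is the censoring assumption. It does not remove the issue, because that assumption is never stated.

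The study tests no hypothesis and warns of low precision. The FAS comparator's interval runs from 1.47/2.32 = 0.63 to 3.65/2.32 = 1.57 times its estimate, wider than the whole assumed bias range. That also stands, though precision and selection are separate matters and the protocol still fixes how similar results are to be read.

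A reader might infer three stronger things:

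- *The comparison sets two different groups of women against each other.* The documents show a whole arm and a subset of it.
- *Returners are known to be lower-risk, so the results will flatter the vaccine.* No return rate or risk contrast is given, and the bias could run either way.
- *The same fault undermines the Cohort 2 conclusion.* Section 3.5.5.1 rests that reading on the base-study GARDASIL group. The Colombian placebo entries in Table 3-4 are context.

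**Conclusion.** The label Cohort 1 carries two meanings, and the similar-incidence reading depends on non-informative non-return that the protocol neither states nor checks. The size and direction of any bias cannot be known from the documents. The range of 0.71 to 1.25 rests wholly on assumed participation of 60-90% and assumed risk ratios of 0.5 to 2, with constant hazard; near-complete return brings it close to 1.00. In the primary PPE population the Cohort 1 comparator stays at 0 cases, so any selection there acts only on the follow-up side. The comparator itself can shift where base-study cases exist, as in FAS. This is a cheap improvement to interpretation and does not invalidate the design.

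**What to change.** - Use separate labels throughout for all Colombian women randomized to GARDASIL and for those who entered the follow-up study, and likewise for the Colombian placebo women.
- Keep the all-randomized comparator in Table 3-4. Add a sensitivity column giving the same base-study incidence in women who entered the follow-up.
- Retain those women's base-study cases in the added column. Applying the Section 2.7 exclusion from Day 1 would force their Day 1 to Year 4 incidence to zero.
- State that similar incidence is read as continuing effectiveness only if both versions agree.

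The cost is one flag and one table column. The added column has fewer cases: of the 18 FAS cases, about 16.2 (0.9 × 18) with 90% return and equal risk, or about 9.7 (776 × 0.7 × 1.78%) with 70% return and k = 2. It also conditions on later return, which a base-study diagnosis may itself influence. It should therefore stand beside the all-randomized comparator and not replace it.
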